### **Study to estimate cost**

A cost study of both paper based and electronic IMCI will be conducted to address the following objective:

**Objective 6:** To compare the economic costs of developing and implementing the new IMCI algorithms when using i) paper based decision charts and ii) electronic decision support algorithms.

This study will collect cost information and develop a model to ascertain the cost per child seen using both e-IMCI and traditional IMCI and then assess the relative cost-effectiveness on a cost per child correctly treated measure of outcome. This is the same measure that was used in the multi country IMCI evaluation done by WHO in Tanzania (Armstrong, 2004) and so provides an excellent basis for comparison. (Tool available at [http://www.who.int/imci-mce/Publications/facility\\_costs.pdf](http://www.who.int/imci-mce/Publications/facility_costs.pdf)) In addition to the cost of seeing a child with an acute febrile illness, we will also collect data on the cost of changing the paper based chart booklet and training the health worker in its use. This will be compared with similar data collected to calculate the costs of reprogramming and training a health worker to use the electronic algorithm.

The study will look at the cost of implementation of both paper and electronic IMCI on the basis of time spent by a clinician and the cost of equipment or supplies. For capital goods such as the PDA or booklet, it will be assumed that the useful life of each is approximately 2 years.

### **Sample size calculation**

**Appropriateness of drug use, provider's adherence and mothers' understanding of prescribed advice (objectives 3, 4 and 7):** The feasibility and adherence study will include 1920 patients (640 per arm). For objectives 3 and 4, this sample size is adequate to detect a significant difference between each arm on the rate of antibiotic prescription assuming that among malaria negative patients (80% of all), 60% will be prescribed antibiotics in the control arm versus 30% in those using the new protocol (intervention groups). For objective 7, this provides 80% power to detect a 20% difference in caretaker comprehension immediately after the clinic visit, at a 0.05 significance level. This large sample size is required taking into account the need for stratification by time period and setting (urban vs rural), as well as the potential heterogeneity due to the randomisation per health facility.

**Assessment of safety study and caretaker adherence to prescribed treatment and advice (objective 5 & 8):** The safety study will include another 2160 patients (720 per arm). This sample size is sufficient to demonstrate equivalence (non-inferiority) of the new algorithm when compared to old IMCI (or routine practice) on the primary outcome assuming a probability of 0.12 of unscheduled reattendance in all arms and an acceptable difference <0.05 (power 80%), with 10% loss of follow-up

(<http://www.ucalgary.ca/~patten/blackwelder.html>). An equivalence study has been chosen since we aim at achieving at least similar health outcomes but with less drug prescribed (antimalarials and antibiotics) with the new IMCI algorithm. The sample is also sufficient for 80% power to detect a 20% difference in caretaker actions one week after the clinic visit, at a 0.05 significance level.

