Objective 5: To assess whether the new IMCI guidelines are equivalent in terms of health outcomes (safety) as the old IMCI guidelines (or usual procedures).

Objective 6: To compare the economic costs of developing and implementing the new IMCI algorithms when using 1) paper based decision charts and 2: electronic decision support algorithms.

Objective 7: To compare health outcomes and mothers' understanding of the diagnosis and treatment requirements for a child after the IMCI visit comparing traditional paper-based IMCI care and eIMCI with enhanced communications.

Objective 8: To compare the mothers' adherence to prescribed advice post-visit between the paper-based IMCI and eIMCI with enhanced communications.

This study will be done as a prospective randomized controlled study in health facilities (government run health centres and dispensaries) that are randomly selected from the total number of sites in Dar es Salaam and Kilombero/Ulanga stratified by location (Dar es Salaam and Kilombero/Ulanga and type of facility (health centre and dispensary). Our initial estimate is to use 24 sites with 8 in each arm of the study.

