#### **Training component**

A formal training on the new IMCI algorithm will be done for all clinicians taking care of patients in the health facilities selected for interventions. In those under a) only paper based decision chart will be used,; in those under b) paper based decision chart will be used first for visualizing and understanding the new algorithm, and then the latter will be removed and replaced by PDAs with formal training on their use. No training, outside advice provided on site when requested, will be undertaken for clinicians under c). The same type of procedures has been used in the previous project (IMALDIA) ([name] 2008a).

**Study to assess appropriate use of drugs, estimation of provider's adherence and mother's understanding of prescribed advice (objective 3, 4 & 7):**

The total sample size will be about 960 patients in Dar es Salaam and 960 in Kilombero/Ulanga (i.e. 1920 patient consultations observed). The randomization will be by site (health facility) rather than by individual patient so that all patients at an individual site will be assessed using either the original IMCI guidelines, the new IMCI paper guidelines or the new IMCI electronic guidelines. The first half of all patients will be done 4 weeks after training and the second half one year after training to investigate the sustainability of the intervention effect overtime.

**Subjects:** All voluntary patients between 2 months and 59 months coming to an outpatient facility in the study with an acute illness.

**Procedures:** Each child between 2 and 59 months brought to a clinic for acute care will be seen by the clinician using the protocols implemented in that particular health facility [original IMCI (or usual practice) or new IMCI paper chart or electronic IMCI protocol] as they would normally. Patient's caretakers will be asked whether they are willing to participate in this study. Those who agree will be read an informed consent script and asked to sign their consent.

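### The 80% power stated for the safety non-inferiority test shows no allowance for randomising health facilities, and falls well short at plausible between-facility correlation

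*Protocol*

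**What the plan says.** The Protocol's Sample size calculation (objectives 5 and 8) sets the safety sample: "The safety study will include another 2160 patients (720 per arm"). It calls this enough to show non-inferiority of the new algorithm on these terms: "assuming a probability of 0.12 of unscheduled reattendance in all arms and an acceptable difference <0.05 (power 80%), with 10% loss of follow-up". A Blackwelder calculator is cited. The paragraph names no alpha for this test, no ICC, no design effect and no number of facilities.

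Under Training component the Protocol says: "The randomization will be by site (health facility) rather than by individual patient". The Study Phase description adds: "Our initial estimate is to use 24 sites with 8 in each arm of the study". The safety study uses the same randomised facilities.

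A remark that facility randomisation may bring heterogeneity does appear in the Sample size calculation. It closes the paragraph on the separate 1920-patient study (objectives 3, 4 and 7), carries no figure, and has no counterpart in the safety paragraph.

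**The concern.** Children seen at one facility share clinicians, catchment and local reattendance habits, so their outcomes are correlated. A calculation for independent children then overstates the power of a facility-randomised comparison, and most of all when there are few facilities per arm.

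Unscheduled reattendance is the primary safety outcome. The Protocol relies on this comparison in its Ethical considerations, to justify the control arm, and in section 3.5, to meet the do-not-harm principle. If real power is nearer one half than 80%, the likely result is an interval that does not exclude the margin, and readers may take that for reassurance.

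**Working it through.** **Inputs from the Protocol.** Reattendance 0.12 in all arms; margin 0.05; power 80%; 720 enrolled per arm; 10% loss; 8 facilities per arm (initial estimate). Evaluable: 720 × 0.9 = 648 per arm, and 648 / 8 = 81 per facility. **Assumed:** one-sided alpha 2.5% or 5%; ICC 0.005 to 0.05; no gain from stratification.

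**Step 1. The plan's own number, independent children.** n per arm = (z_alpha + z_power)² × 2 × 0.12 × 0.88 / 0.05².
- One-sided 2.5%: (1.960 + 0.842)² × 0.2112 / 0.0025 = 663 evaluable. Adding 10% gives 729; dividing by 0.9 gives 737. The plan has 720.
- In reverse, 648 evaluable give SE = √(0.2112 / 648) = 0.01805 and power Φ(0.05 / 0.01805 − 1.960) = 79%. The largest design effect compatible with 80% is 648 / 663 = 0.98, so there is no room for clustering.
- One-sided 5%: 522 evaluable, 580 enrolled. The largest design effect is 648 / 522 = 1.24, and (1.24 − 1) / 80 = 0.003 is the largest ICC by normal approximation. With t on 14 df it is 0.0015.

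**Step 2. Clustered power.** Design effect = 1 + 80 × ICC.
- One new arm against control: SE = √(0.1056 × DE × 2 / 648), noncentral t with 16 − 2 = 14 df.
- Pooled a+b against c: SE = √(0.1056 × DE × (1/1296 + 1/648)), 24 − 2 = 22 df.
- Noncentrality is 0.05 / SE. Example, pairwise at ICC 0.01: DE = 1.80, SE = 0.0242, noncentrality 2.06.

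Power at one-sided 2.5% [5%]:

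| ICC | DE | One arm vs control | Pooled a+b vs c |
|---|---|---|---|
| 0.005 | 1.40 | 58.7% [71.9%] | 73.3% [83.5%] |
| 0.01 | 1.80 | 48.5% [62.5%] | 62.5% [74.7%] |
| 0.02 | 2.60 | 36.0% [49.6%] | 47.5% [60.9%] |
| 0.05 | 5.00 | 21.0% [32.1%] | 27.7% [39.8%] |

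The normal approximation is somewhat kinder: pairwise at ICC 0.01 it gives 54% [66%].

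**Step 3. Scale of the assumed ICC.** At a mean of 0.12, ICC 0.01 corresponds to a between-facility SD of √(0.01 × 0.1056) = 0.032, or 3.2 percentage points.

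**Step 4. Margin supportable at 80% power, pairwise, same t test.** One-sided 2.5%: 7.3 points at ICC 0.01 and 12.2 at ICC 0.05. One-sided 5%: 6.3 and 10.6.

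**Step 5. Can more children per facility repair it?** With 8 facilities per arm (pairwise, one-sided 2.5%, normal approximation), 663 × ICC must stay below 8. Beyond an ICC of about 0.012, no number of children per facility reaches 80%.

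**The case against.** **Alpha is not stated.** The match to 720 at one-sided 2.5% is an inference. At one-sided 5% the plan carries some slack, and 80% survives on the pairwise contrast up to an ICC of 0.003 (normal) or 0.0015 (t). This stands and is why both alphas are shown. The text does not present the slack as a clustering allowance.

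**The contrast is not fixed.** Objective 5 concerns the new guidelines, and Phase 3 compares arms a) and b) with c), so pooling is a permissible reading. On that reading, by t with 22 df, 80% holds up to an ICC of about 0.0024 at one-sided 2.5% and 0.007 at 5%. A reader might infer from the pairwise result that 80% is out of reach at any ICC at one-sided 2.5%; that is true only of the pairwise contrast.

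**ICC, stratification and follow-up.** The size of the shortfall rests on an assumed ICC. Stratification by location and facility type may recover some between-facility variance, but the calculation claims no such credit. Using the 97% follow-up of the earlier study in place of 90% raises independent-child power only to 82% at one-sided 2.5%.

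**Two stronger readings are not supported.** One is that the same paragraph's caretaker claim, "The sample is also sufficient for 80% power to detect a 20% difference in caretaker actions one week after the clinic visit", contradicts the safety calculation by implying a much larger design effect. It is an at-least statement about a second endpoint. A sample sized for a 5-point margin will naturally exceed the need for a 20-point difference, and it implies no design effect. Nor need the two outcomes share an ICC. The other is that this test is the only evidence of safety: cure at day 7 and delayed complications are listed as secondary outcomes.

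**Conclusion.** The point holds in this form: the stated 80% has no visible allowance for facility randomisation, and the test that would deliver it is not specified. At an ICC of 0.01 the power is 48.5% [62.5%] pairwise and 62.5% [74.7%] pooled, at one-sided 2.5% [5%]. At that ICC and above, 80% is missed at either alpha and on either contrast. Below it, the answer depends on which alpha and contrast were meant: pooled at one-sided 5% still reaches 83.5% at ICC 0.005. These figures assume 8 facilities per arm, 81 evaluable children each, a true difference of zero and no gain from stratification. The direction of the error is firm. Its size depends on an ICC that the Protocol does not give.

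**What to change.** Replace the 80% sentence in the Sample size calculation with a cluster-based statement. It should name the one-sided alpha, the number of facilities per arm and evaluable children per facility, the contrast, and an ICC range with its source. It should then give the resulting power, or the margin supportable at 80%. The reattendance ICC need not be the one used for caretaker outcomes. This costs only wording, but the stated power becomes less favourable.

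Two further options are design choices, not edits:
- **Name pooled a+b against c as the main safety contrast**, with arm-specific intervals always shown because pooling can hide a difference between paper and electronic formats. At one-sided 2.5% and ICC 0.01 this lifts power from 48.5% to 62.5% with no extra children. It does not restore 80%.
- **Add facilities**, since 24 is only an initial estimate. For the pairwise contrast at one-sided 2.5% and ICC 0.01, 663 × 1.80 / 81 = 14.7, so about 15 per arm by normal approximation, and somewhat more with a t test. This adds field cost.

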### **2.5.2.3 Phase 3: Analysis and writing**

The analysis will focus on answering the three research questions.

*1. Can we improve IMCI protocols to be more specific about the use of antimalarial drugs and antibiotics for febrile illness?*

This will be analyzed by comparing the results of arm a) and b) against control arm c) to determine whether the new protocols do improve the overuse of anti-malarials and antibiotics (primary outcome: rate of children being prescribed antibiotics).

*2. Is the use of electronic algorithms more or less effective and efficient than papers based algorithms in implementing these changes in a field setting?*

This will be analyzed by comparing the results of arms a) with b) to determine the adherence of health workers to the protocols using paper based or electronic algorithms, as well as costs (primary outcome: appropriate diagnosis classification and use of antimalarials and antibiotics).

*3. Is the use of new IMCI algorithms aimed at reducing overuse of antimalarials and antibiotics as safe as old IMCI protocols( or routine practice)?*

This will be analyzed by comparing the results of arms a) and b) with control arm c) to determine whether the new protocols leads to similar health outcomes (equivalence study) (primary outcome: unscheduled reattendances).

*4. Can we improve IMCI protocols to improve clinician messaging communications so that caretakers better understand instructions for care of the child and subsequently adhere to prescribed advice to caretakers such that patient outcomes improve?*

The analysis will be done by comparing the results of arm b) with the paper arm a) and control arm c) to determine whether the electronically enhanced communications between health worker and caregiver leads to an improved understanding by the caregiver of what medicines to give the child and whether this leads to improved health outcomes.

### **2.5.2.5 Ethical considerations**

The project has been already discussed in depth with the different partners, including the ethical considerations. When a project is aiming at improving adherence to universally accepted recommendations such as IMCI guidelines, there is no definite harm to be expected. On the reverse, there is a hope that patients, and especially children will benefit from the intervention planned. The usual criticism of PDA-assisted diagnosis and treatment is that clinicians may feel less concerned and may not investigate the peculiarities of the patients they have to care. However, we have seen during our previous project that the level of care is very poor and it is unlikely that such a tool could lead to worse care. What has been observed in the past with such tools is that the clinicians tend to acquire an automatism that is beneficial for the patient, as long as the automatism complies with updated guidelines, which will be the case for yours. These tools are also very useful as a teaching and training material. If the expert feels that the safety of the child is compromised (e.g. diagnosis of pneumonia but no antibiotics prescribed), the expert will adapt the prescription (e.g. add anti-infective drugs).

The choice to include a control arm (in this instance usual procedures of the health facility) should always be questioned, especially so when the quality of care is known to be below standard. However, the control group is critical in our study to ensure safety of the new IMCI-derived algorithm. Without control arm, we may miss a deleterious effect of the new algorithm on health

outcomes. It is also important to document the impact on the number of drugs prescribed: reducing drug intake is indeed an essential aspect of safety. Lastly, the inclusion of a control group allows a refined assessment of the effectiveness of i) training and supervision of the use of a new algorithm, ii) same but based on an electronic support rather than paper.

Eligible patients and their caretaker will be read an information sheet so that they can give their informed consent if they agree to participate in the study.. The project will be conducted in health facilities selected by the DSM City Council City Medical Office of Health or the District Medical Office in Kilombero/Ulangua and where the person in charge and the staff agree.

## 2.6 List of individual tasks and responsibilities of the partners (see also section 3.4)

| Results                                                                                 | Activities foreseen to reach the results                              | Indicators with milestones (in months from project start)                                               | Responsible project partner                                      |
|-----------------------------------------------------------------------------------------|-----------------------------------------------------------------------|---------------------------------------------------------------------------------------------------------|------------------------------------------------------------------|
| R1: Computerization of new IMCI e-algorithm and training material                       |                                                                       |                                                                                                         |                                                                  |
|                                                                                         | A 1.3: Design of new IMCI algorithm                                   | I 1.3.1: New IMCI algorithm (6 months)                                                                  | STI (collaboration with IHI and CMOH)                            |
|                                                                                         | A.1.4 Development of paper based decision chart and training material | I 1.4: Paper decision charts and training brochures (6 months)                                          | IHI & CMOH (collaboration with STI)                              |
|                                                                                         | A.1.5: Computerization of new IMCI algorithm                          | I 1.5: Computerized new IMCI algorithm (6 months)                                                       | D-Tree (collaboration with IHI and STI)                          |
|                                                                                         | A1.6: Addition of messages from HW to mother in eIMCI algorithm       | I 1.6: New eIMCI algorithm with improved messaging incorporated (6 months)                              | Harvard School of Public Health (collaboration with IHI and STI) |
| R2: Training of clinicians for new IMCI paper and e-IMCI protocols in intervention arms | A.2.1: Training of clinicians                                         | I 2.1: Clinicians from intervention arms trained for new IMCI paper protocols and e-IMCI (12 months)    | CMOH (Dar es Salaam), IHI (K/U districts)                        |
| R3: Adherence and appropriate use of drugs                                              | A.3.2: Observation and assessment of 1920 patients consultations      | I 3.2: Diagnostic classification, appropriate prescription of antimalarials and antibiotics (30 months) | CMOH (Dar es Salaam), IHI (K/U districts)                        |
| R4: Safety of new IMCI algorithm                                                        | A.4.1: Follow-up of 2160 patients                                     | I 4.1: Unscheduled reattendance (24 months)                                                             | CMOH (Dar es Salaam), IHI (K/U)                                  |
| R5: Costs                                                                               | A.5.1: Costing of 300 children                                        | I.5.1: Cost (27 months)                                                                                 | CMOH (Dar es Salaam), IHI (K/U districts)                        |
| R6: Conference abstracts and papers                                                     | A.6.1: Analysis and writing                                           | I.6.1: Accepted abstracts and papers                                                                    | STI, IHI, CMOH                                                   |

### *Swiss Tropical Institute:*

**Tasks:** Development of the updated decision tree (IMCI-derived); training and field activity support; support for data analysis and writing;

**Responsibilities:** Overall project coordination; knowledge transfer; academic support; accountability to the funding agency.

### *Ifakara Health Institute:*

**Tasks:** Development of chart booklet and training material (with STI and CMOH); training of health staff (with STI and CMOH); implementation of PDAs and chart booklet assisted diagnosis and treatment in selected health facilities of K/U; observation and evaluation of consultation processes;

data entry and cleaning; data analysis and writing with support of STI.

**Responsibilities:** Overall project coordination in the field; conduct of the project on the ground in K/U districts with support of STI; accountability to the STI for expenses in Tanzania.

***Dar es Salaam City Council City Medical Office of Health***

**Tasks:** Development of chart booklet and training material (with STI and IHI); training of health staff (with STI); implementation of PDAs and chart booklet assisted diagnosis and treatment in selected health facilities of Dar es Salaam; observation and evaluation of consultation processes; data analysis and writing with support of STI.

**Responsibilities:** Conduct of the project on the ground in Dar es Salaam with support of IHI and STI.

